### Atorvastatin protocol

Open-label atorvastatin will be administered according to the following protocol. A dosage of 80 mg administered orally daily will commence immediately after randomization (within two hours and prior to surgery) and will continue until discharge (unless otherwise indicated according to history and lipid profile). A liver function test and creatinine kinase levels will be monitored to assess side effects.

### Electrocardiography protocol

A digital 12-lead ECG will be recorded preoperatively and on postoperative days 1, 2 and 3 and assessed for heart rate, PR interval, QRS duration and morphology, Q waves, QT duration and QTc, as well as ST-T morphology and overall interpretation to look for changes that meet the universal definition of myocardial infarction.

### Echocardiography protocol

A transthoracic echocardiogram will be done on every patient prior to discharge to assess for evidence of regional wall motion abnormality, systolic and diastolic dysfunction. Images of the left ventricle in motion and hemodynamic measures will be recorded at rest.

### Holter protocol

Continuous 48-hour Holter monitoring will be commenced within 24 hour postoperatively to assess for heart rate, postoperative arrhythmia including atrial fibrillation, its frequency and its duration.

### CT coronary calcium protocol

A non-invasive, non-contrast CT coronary calcium score will be acquired on a 320-detector row CT scanner (Toshiba Aquilion ONE, Toshiba Medical Systems, Otawara, Japan) prior to or at discharge following surgery. The scan range will be planned between the carina and cardiac apex. Depending on the expected scan range, a 320 × 0.5 mm or a 280 × 0.5 mm detector configuration will be used as previously described [91]. Immediately before image acquisition, an optimal reconstruction phase will be automatically determined during a breath hold exercise with ECG-recording by use of cardiac scanning software (SureCardio, Toshiba Medical Systems, Otawara, Japan). Full cardiac calcium score acquisition will be performed in a single gantry rotation (0.35 seconds) during breath hold at inspiration that allows image reconstruction at a single cardiac phase. Scan parameters: tube voltage 120 kV and tube current 200 to 400 mA (dependent on patient size and shape as visually assessed by the radiology technician: 200 mA for small and/or thin patients, 250 mA for normal patients and 300 to 400 mA for large and/or obese patients).

Image reconstruction will be performed using a standard reconstruction kernel filter from the cardiac scanning software (SureCardio, Toshiba Medical Systems, Otawara, Japan) with a 200 to 220 mm^2^ field of view. Non-overlapping 0.5 mm datasets will be reconstructed for evaluation of coronary calcium, and the reconstructions transferred to a post-processing workstation for analysis.

Calcium volume scores (Table 1) will be performed on a post-processing workstation (Vitrea FX, version 1.0, Vital Images, Minnetonka, United States), using calcium score analysis software (VScore, Vital Images). Coronary calcium will be defined as an area of at least three ‘face-connected’ voxels in the axial plane in the course of a coronary artery, with an attenuation threshold-value of ≥130 Hounsfield units (HU).

**Table 1 Tab1:** **Calcium score interpretation**

Translation of calcium score		
Calcium score	Implication	Risk of coronary artery disease
0	No identifiable plaque	Very low, generally less than 5%
1 – 10	Minimal identifiable plaque	Very unlikely, less than 10%
11 – 100	Definite, at least mild atherosclerotic plaque	Mild or minimal coronary narrowings likely
101 – 400	Definite, at least moderate atherosclerotic plaque	Mild coronary artery disease highly likely, significant narrowings possible
401 or higher	Extensive atherosclerotic plaque	High likelihood of at least one significant coronary narrowing

### Troponin I

Serum for troponin I measurement will be taken preoperatively (within two hours of randomization) and on days 1, 2, 3 and 4 postoperatively. Serum will be stored at -70°C. Prior to analysis, the frozen serum will be thawed, thoroughly mixed and re-centrifuged.

Troponin I will be measured using the Architect STAT Troponin I assay (Abbott Diagnostics, Abbot Park, IL, USA). The 99th percentile of a healthy reference population using this assay has been previously established at 0.03 mcg/l and levels above this are considered indicative of myocardial injury. The coefficient of variation (CV) for this assay is 10% at the 99th percentile.

### Markers of cardiovascular stress

Levels of MR-proANP, MR-proADM and CT-proET-1 will be determined using the Time-Resolved-Amplified-Cryptate-Emission (TRACE) technology on the Kryptor Compact analyzers (BRAHMS GmbH, Henningsdorf, Germany), from samples collected at the same time points as troponin.

T-pro-BNP levels will be measured using the Elecsys electrochemiluminescence immunoassay (ECLIA) proBNP II assay on a Roche Cobas E170 analyzer (Roche, Indianapolis, IN), from samples collected at the same time points as troponin. This assay uses two polyclonal antibodies that recognize epitopes located on the N-terminal part of pro-BNP. The lower limit of the detection range (sensitivity) is 5 pg/ml. Within-run coefficients of variation are 1.9% at a concentration of 64 pg/ml and 1.3% at 14,142 pg/ml. Total precision coefficients of variation are 3.1% at a concentration of 36 pg/ml and 2.7% at 125 pg/ml. Levels of the biomarkers of the renin-angiotensin pathway, including Ace2, will be measured.

### Markers of plaque burden

Total cholesterol, triglycerides, HDL and LDL will be measured at randomization (fasting sample just prior to surgery) and again on day 2 postoperatively (fasting sample), using the same venipuncture as the preoperative and day 2 troponin measurement.

sPLA2 and Lp-PLA2 mass and activity assays will be performed at the same time point as fasting lipids. Lp-PLA2 and sPLA2 mass will be measured with an ELISA based assay (sPLA2: Cayman Chemical Co., Ann Arbor, Michigan, United States and Lp-PLA2: diaDexus Co. California, United States). sPLA2 activity is measured by a fluorometric assay. All blood samples will be collected and put on ice prior to centrifugation, separation and storage at –80°C in a dedicated secure freezer. Batch testing will then be performed at a later date.

### Follow-up protocol

All patients will be followed up on by means of a semi-structured interview (via telephone call) at 30 days, 6 months and 1 year, enquiring about any cardiac events, hospitalizations, functional level and medication usage. Additionally their medical records will be retrieved and/or primary physician contacted for more information. Deaths will be confirmed with the Births, Marriages and Deaths registry.

### Sample size calculation

We estimated that 200 patients (calculated sample size of 171) would be required to have a power of 0.90 (alpha = 0.05, two tail) to identify a difference(moderate effect size (f = 0.25) in PMI incidence between the 4 groups. (F test Anova:fixed effects,special,main effects and interactions; Analysis: a priori).

We plan to recruit 200 patients in total (50 in each treatment cell), providing an actual power of 0.94 to detect a moderate effect size.

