## Methods/Design

This is a prospective, single-centre (Northern Hospital, Victoria, Australia), open-label, 2x2 factorial, randomized controlled trial of ivabradine and atorvastatin in the prevention of myocardial injury following emergent orthopedic surgery for lower limb fracture. The Northern Hospital Ethics Committee approved this study on 6 July 2012 (reference number HREC P06/12). This study complies with the Declaration of Helsinki. Informed consent will be obtained from all participating patients. Upon signing informed consent, the patient’s data will be populated as per protocol.

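### The sample size of 171 and the powers of 0.90 and 0.94 hold for a 1-df factorial effect, not for the four-group difference to which the text attaches them

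*Protocol article*

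**What the plan says.** The Methods/Design section describes an "open-label, 2x2 factorial, randomized controlled trial of ivabradine and atorvastatin", with four equally sized arms. The Sample size calculation section sets a "power of 0.90 (alpha = 0.05, two tail") and states the target as being "to identify a difference(moderate effect size (f = 0.25) in PMI incidence between the 4 groups". It reports a calculated size of 171 and a planned size of 200, 50 per cell, the latter "providing an actual power of 0.94 to detect a moderate effect size". In parentheses it names the procedure used: "F test Anova:fixed effects,special,main effects and interactions; Analysis: a priori". It does not give the numerator degrees of freedom, which that procedure needs as an input, and it does not translate f into event rates.

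**The concern.** A difference among four groups is a hypothesis with 3 numerator degrees of freedom. Each main effect of a 2x2 factorial, and its interaction, has 1. At the same f and the same N the two have different power, so one figure cannot serve both unless the section says which is meant. The section words the first and appears to have computed the second.

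The reader is told that the trial has a 6% chance of missing an effect of the stated size. For the comparison as worded, at that overall effect size, the chance is about 15%, and 200 patients do not reach even the 0.90 target. Someone planning the analysis from this section could also take the four-arm comparison as the powered one and overlook the 100 versus 100 contrast for each drug, which is where the factorial design has its strength.

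A second difficulty is that f is a standardised effect for means, while the target is an incidence. Without event rates, a reader cannot judge how large an effect the label of moderate stands for.

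**Working it through.** **Inputs** (Sample size calculation section unless noted): alpha 0.05; f = 0.25; target power 0.90; N = 171 calculated and 200 planned; four cells, 1:1:1:1 (Randomization protocol section).

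**Formula.** Fixed-effects ANOVA: noncentrality lambda = f² × N, numerator df u, denominator df N − 4. Power is the probability that a noncentral F(u, N − 4, lambda) exceeds the 95th percentile of the central F(u, N − 4).

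lambda = 0.0625 × 171 = 10.69 at 171, and 0.0625 × 200 = 12.5 at 200.

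**Step 1: reproduce the plan's figures.**

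| Numerator df | Power at 171 | Power at 200 | N for 0.90 |
|---|---|---|---|
| 1 | 0.9015 | 0.9404 | 171 |
| 2 | 0.835 | 0.891 | 206 |
| 3 | 0.781 | 0.848 | 231 |

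Only u = 1 returns 171, 0.90 and 0.94. Using 2 or 8 groups in place of 4 in the denominator df does not change this.

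**Step 2: the comparison as worded (u = 3).** Power is 0.848 at 200, so the chance of a miss is 1 − 0.848 = 0.152, against 1 − 0.94 = 0.06 as stated. Power 0.90 needs 231 patients (232 with equal cells), 31 more than planned. Power 0.94 needs 267. With 200 patients, the 3-df test reaches 0.90 only at an overall f of about 0.269.

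**Step 3: check on a binary outcome.** A simulation with one active drug and 52.9% versus 29% gave about 0.94 for the 1-df chi-square and about 0.84 for the 3-df chi-square. The gap does not come from using ANOVA for a proportion.

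**Step 4: dependence on the scenario.** In a balanced factorial without interaction, the overall f² is the sum of the two main-effect f².
- One drug works at f = 0.25 and the other does nothing: overall f = 0.25, and the 3-df power at 200 is 0.848.
- Both drugs work at f = 0.25: overall f = √(0.0625 + 0.0625) = 0.354, lambda = 0.125 × 200 = 25, and the 3-df power is about 0.99 at 200 (0.98 at 171).

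**Step 5: what f = 0.25 means as an incidence.** For two equal groups, f = (|p1 − p2| / 2) / √{[p1(1 − p1) + p2(1 − p2)] / 2}. Solving for p2 at f = 0.25, with the control rate p1 as an assumption:

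| Assumed control rate | Rate on treatment | Difference |
|---|---|---|
| 52.9% | about 29% | about 24 points |
| 40% | about 18% | about 22 points |
| 30% | about 11% (10.5%) | about 19 points |

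Check of the first row: numerator (0.529 − 0.290)/2 = 0.1195; denominator √[(0.2492 + 0.2059)/2] = 0.477; ratio 0.25. The 52.9% is the troponin-elevation rate in the earlier urgent orthopedic cohort described in the Background. The other two rates are illustrative.

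**The case against.** The strongest reply is that the section itself names main effects and interactions as the procedure, and in a 2x2 design each of these has 1 df. The figures are therefore right for the test that was run. The Discussion also gives each drug its own hypothesis. This stands: the sample size is not miscalculated. It does not rescue the sentence, because the only hypothesis written there is the four-group one and the df is not stated.

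A reader might infer that the trial is underpowered, or that it gives up the efficiency of its factorial design. The document does not support either. No section prescribes a 3-df primary test, and the primary model may well be set out in an analysis plan that is not shown. The value 0.85 also depends on an overall four-cell f of 0.25. If both drugs work at f = 0.25 each, as the Discussion hopes, the four-group test has about 0.99.

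A reader might also take 52.9% versus 29% as the effect this trial was designed to find. The article does not give 52.9% as its control rate, and patients with raised troponin before surgery are excluded, so the rate here may differ. Borrowing the relative reduction from the beta-blocker trial cited in the Background, to argue for low power, would carry over an effect from another drug class and from infarction as the outcome. It says nothing firm about this trial.

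Finally, the primary outcome is both a frequency and a magnitude of myocardial injury, and f suits the magnitude. That is fair, but the section ties f to incidence.

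**Conclusion.** The point holds as a mismatch between number and hypothesis. The figures 171, 0.90 and 0.94 are correct for a 1-df effect at f = 0.25 and alpha 0.05. A main effect is the natural reading, though the interaction fits equally well. They are not correct for a four-group comparison at overall f = 0.25, where power is about 0.85 at 200 and 0.78 at 171.

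The result rests on equal cells, the noncentral F approximation (supported by the binary simulation), and f meaning the overall effect across the four cells when the four-group wording is taken literally. Severity is should-fix: a printed power is attached to a comparison that lacks it, but the design, the allocation and the recruitment target are unaffected.

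**What to change.** Keep N at 200 and revise the Sample size calculation section as follows.

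1. Replace the four-group target with the two marginal main effects: ivabradine yes/no and atorvastatin yes/no, each 100 versus 100 (two cells of 50 on each side), estimated from one model containing both factors.
2. State the numerator df of 1, and that 171 patients give 0.90 and 200 give 0.94 for each main effect at f = 0.25.
3. If a four-group test is kept, call it secondary and give its power as about 0.85 at 200 for an overall f of 0.25.
4. Show f = 0.25 as incidences over a range of control rates labelled as assumptions (about 53% versus 29%, 40% versus 18%, 30% versus 11%), not as a single design value.

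The cost is a few sentences of rewording and a less favourable figure for the four-group comparison. No extra patients are needed and nothing changes in randomization.

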### Myocardial stress (myocardial oxygen supply-demand imbalance) and role of ivabradine

Studies suggest that tachycardia is the most common cause of postoperative oxygen supply-demand imbalance leading to PMI [16, 17]. Numerous studies using perioperative Holter monitoring in patients undergoing major surgery have shown that asymptomatic, heart rate related ST segment depression is common postoperatively and associated with in-hospital [18, 19] and long-term morbidity and mortality [20]. Postoperative cardiac complications, including sudden death, occur after prolonged silent ST segment depression [11, 16, 21–25]. Furthermore, peak troponin elevation correlates with the duration of ST segment depression [16].

These studies are the basis for trials examining the use of perioperative beta-blockers to reduce the incidence of postoperative cardiac events. Initial small studies were promising [5, 26], however other moderate-sized randomized trials failed to show benefit [27, 28]. A subsequent meta-analysis of non-cardiac surgery randomized controlled trials did suggest a benefit for beta-blockers in the reduction of cardiovascular events, but showed an increased risk of hypotension and bradycardia [29]. The largest randomized controlled trial to date, the POISE trial (Effects of extended-release metoprolol succinate in patients undergoing non-cardiac surgery), randomized 8,351 patients at increased risk of cardiovascular events to receive metoprolol or placebo [30]. The group assigned to metoprolol showed a reduction in myocardial infarction (4.2 versus 5.7%, *P* = 0.002), however there was an increase rate of stroke (1.0 versus 0.5%, *P* = 0.005) and death (3.1 versus 2.3%, *P* = 0.03) in the treatment group. Clinically significant hypotension occurred in 625 patients (15%) in the metoprolol group. This higher incidence of clinically significant hypotension has been postulated as the cause for the occurrence of more strokes and deaths.

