### Novel cardiac biomarkers

Elevated levels of circulating biomarkers related to cardiac volume, pressure overload and cardiovascular stress offer insights into subclinical cardiac stress and thus have the potential to aid in risk stratification and provide mechanistic data on disease prevention measures [57]. Specifically, B-type natriuretic peptide (BNP; either the hormone or the aminoterminal fragment of the prohormone (NT-proBNP)) is a counter-regulatory hormone released predominantly from ventricular myocytes in response to ventricular dysfunction, stretching, increased wall tension and ischemia. Elevated levels of BNP have been shown to predict mortality and heart failure events across a broad range of individuals, ranging from the general population to patients with coronary disease or heart failure [57–63]. We recently showed that elevated NT-proBNP levels pre- and postoperatively are independent predictors of in-hospital cardiac events and two-year mortality [64].

Development of newer assays that target more stable epitopes of hormones or prohormones that are released in relation to cardiomyocyte and/or vascular stress offers the potential for more refined risk assessment [65]. Specifically, atrial natriuretic peptide (ANP) is a vasodilator and natriuretic that is synthesized in the myocardium in response to increased wall tension [66]. Adrenomedullin (ADM) is a potent vasodilator synthesized in the adrenal medulla, vascular endothelial cells, heart and elsewhere in response to physical stretch and specific cytokines, with levels in the heart elevated in the setting of pressure and volume overload [67, 68]. Endothelin-1 (ET-1) is a potent vasoconstrictor and profibrotic hormone that is secreted by vascular endothelial cells, with levels correlating with shear stress and pulmonary artery pressure [69]. In patients with stable coronary artery disease and preserved left ventricular ejection fraction, elevated levels of these novel biomarkers can help identify patients who are at higher risk of cardiovascular death and heart failure [65]. Higher levels of these three biomarkers have been associated with an increased risk of death and/or heart failure events in patients with established heart failure [70–72].

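### The only arm comparison named for the primary outcome carries no covariates; prespecifying age and heart rate at randomisation would be a low-cost gain in precision

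*Protocol article*

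**What the plan says.** The Primary outcome measure section defines new myocardial injury from peak postoperative troponin I in two forms, a yes/no frequency and a continuous magnitude. The Sample size calculation section seeks a "power of 0.90 (alpha = 0.05, two tail" test for a "moderate effect size (f = 0.25) in PMI incidence between the 4 groups", gives a "calculated sample size of 171", and describes 200 patients as "providing an actual power of 0.94 to detect a moderate effect size". The test family is named there in parentheses: "F test Anova:fixed effects,special,main effects and interactions; Analysis: a priori". No covariate is mentioned.

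The Statistical analysis section lists descriptive summaries, Spearman correlations between biomarkers, a Cox model relating biomarkers to outcomes, and a significance threshold. It describes no comparison between arms. The Randomization protocol describes blocks of variable size and mentions no stratification.

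Age is an inclusion criterion. Heart rate before randomisation is an exclusion criterion and is also used in the ivabradine protocol. NT-proBNP is measured "from samples collected at the same time points as troponin".

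**The concern.** The document itself points to prognostic information that the named test does not use. The Novel cardiac biomarkers section says: "We recently showed that elevated NT-proBNP levels pre- and postoperatively are independent predictors of in-hospital cardiac events and two-year mortality". The section on myocardial stress reports that "tachycardia is the most common cause of postoperative oxygen supply-demand imbalance leading to PMI". With 200 patients in four cells and no stratification mentioned, unexplained variation between patients goes into the error term, and nothing stated protects against chance imbalance in these variables. A test that includes baseline prognostic variables usually gives narrower confidence intervals for both drug effects at no cost in patients. At stake is some precision, plus the credibility that comes from fixing covariates in advance in an open-label trial.

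**Working it through.** **Inputs from the Sample size calculation section.** f = 0.25, alpha = 0.05, four cells, N = 171 for power 0.90, and N = 200 for power 0.94.

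**Reproducing the stated figures.** Use the non-central F distribution with noncentrality λ = N·f², 1 numerator degree of freedom and N − 4 denominator degrees of freedom.
- N = 171: λ = 171 × 0.0625 = 10.69, power 0.9015. N = 170 gives 0.8999, so 171 is the smallest N that reaches 0.90.
- N = 200: λ = 200 × 0.0625 = 12.5, power 0.9404.

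Both figures reproduce as a 1-df test with no covariates. With 2 or 3 numerator degrees of freedom, power at N = 200 is 0.891 or 0.848, and neither matches.

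**Adding covariates.** If q covariates explain a share R² of the variance left by the factorial model, then λ = N·f²/(1 − R²), with N − 4 − q denominator degrees of freedom. The document gives no R², so a range is assumed. To the precision shown, q = 2 (age, heart rate) and q = 3 (with NT-proBNP) give the same results.

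| Assumed R² | Power at N = 200, f = 0.25 | N for power 0.90, f = 0.25 | Power at N = 200, f = 0.20 | Power at N = 200, f = 0.15 |
|---|---|---|---|---|
| 0 | 0.940 | 171 | 0.80 | 0.56 |
| 0.05 | 0.951 | 162 | 0.82 | 0.58 |
| 0.10 | 0.960 | 154 | 0.84 | 0.60 |
| 0.20 | 0.976 | 137 | 0.88 | 0.66 |
| 0.30 | 0.988 | 120 | 0.92 | 0.71 |

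The values f = 0.20 and 0.15 are assumptions of this review, not planned effects.

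**Check on a binary outcome.** The Background reports troponin elevation in 52.9% of patients in an earlier urgent orthopaedic series. Taking that as the rate without the drug, f = 0.25 on one margin of the factorial means a fall to about 29.0%: (0.529 − 0.290)/2 divided by the square root of the mean of 0.529 × 0.471 and 0.290 × 0.710 gives 0.25. In 1,500 simulated trials per setting (linear model, one covariate), unadjusted power was 0.93 to 0.94. Adjusted power was 0.936 with a covariate of no value, and 0.948, 0.959 and 0.977 at R² of about 0.06, 0.12 and 0.21. This agrees with the table.

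**Are the covariates pre-treatment?**
- Age and heart rate at randomisation: yes, by the eligibility criteria.
- NT-proBNP: not established. It shares the troponin samples. The Troponin I section puts the preoperative sample within two hours of randomisation, and the ivabradine and atorvastatin protocols put the first dose in the same two hours. The Markers of plaque burden section takes fasting lipids from that same venipuncture and places it shortly before surgery, which may be up to 48 hours away. The exclusion of patients with raised preoperative troponin suggests an earlier draw. The document does not settle the order.

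**What a post-dose draw could cost.** Assume R² = 0.20, all from NT-proBNP, so its within-arm correlation with the outcome is √0.20 = 0.447. Assume a true drug effect of 0.5 SD (f = 0.25), and that the drug has already lowered the sampled NT-proBNP by δ SD. The adjusted estimate is then 0.5 − 0.447δ.
- δ = 0.12: estimate 0.446, power 0.940. The whole gain is lost.
- δ = 0.20: estimate 0.411, which is 18% too small, and power 0.90, below the unadjusted 0.94.

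**The case against.** The strongest reply is that the ANOVA is a label in a power calculation, not a declared primary analysis. Sizing a trial without covariates is compatible with an adjusted analysis, and covariates are commonly left to a full protocol or SAP, neither of which is shown. This stands. A reader might infer that the plan commits to an unadjusted primary analysis and throws precision away. The document does not say so; it neither plans nor excludes covariates. What remains is that the one arm comparison it names has none.

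The predictors are also less firmly supported than they first appear. The document nowhere calls age a predictor of PMI. The tachycardia statement concerns postoperative supply-demand imbalance, not heart rate at randomisation. The NT-proBNP statement concerns cardiac events and mortality, not peak troponin. Eligibility limits on age, heart rate and preoperative troponin may further reduce the attainable R². All of this stands, and it is why R² has to be an assumed range that includes zero.

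A reader might also take preoperative NT-proBNP to be a covariate without a downside. The documents do not support that: the draw may follow the first dose, NT-proBNP is a listed secondary outcome, and the Discussion expects ivabradine to lower it.

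Finally, one might suppose that power is lost because troponin is analysed on its raw scale. The document states no scale for that analysis, so no such loss can be charged to it.

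**Conclusion.** The point holds as an efficiency recommendation. The only arm comparison named for the primary outcome has no covariates, while age and heart rate at randomisation are already recorded before treatment. At the planned f = 0.25 the gain is about 1 to 5 percentage points of power for assumed R² of 0.05 to 0.30, starting from 0.940. Equivalently, the N needed for power 0.90 falls from 171 to between 162 and 120. It is larger for smaller effects: at f = 0.15, power goes from 0.56 to between 0.58 and 0.71. There is no gain at R² = 0, and the degrees of freedom spent cost almost nothing. These figures rest on a linear-model approximation and on an R² that the document does not supply. They do not show that the trial is underpowered or that its sample size is wrong.

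**What to change.** State in the analysis section that each form of the primary outcome will be analysed with the factorial model already named (two drug main effects and their interaction), adjusted for age and heart rate at randomisation as continuous covariates. Then specify:

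- **Injury (yes/no):** logistic regression, reporting the standardised risk difference for each drug.
- **Magnitude:** a linear model on log peak troponin I with the same covariates.
- **NT-proBNP:** add log preoperative NT-proBNP only where the sample is confirmed to have been drawn before the first study-drug dose. Reconcile the sampling times in the Troponin I and Markers of plaque burden sections so that this can be verified.
- **Sensitivity analysis:** the unadjusted comparison.

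For age and heart rate the cost is wording only, since both are already collected. NT-proBNP also requires a check of draw times against dose times. The article reports the trial as still recruiting, so the covariates should be fixed before outcome data by arm are examined.
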